#### Control group

Participants in the control group will perform the prescribed rehabilitation plan at home. Their rehabilitation status will be monitored through regular online follow-ups, and telephone guidance will be provided if issues arise. After 8 weeks, they will continue the home-based rehabilitation as per the protocol. At each postoperative follow-up visit, the next phase of home-based training will be explained, and precautions will be reviewed.

Both groups will follow the same conventional rehabilitation protocol, with sessions lasting 30 min each, 4–5 times per week. The detailed protocol is presented in Table 2.

**Table 2 T2:** Postoperative rehabilitation protocol for ACLR patients.

Postoperative Time	Rehabilitation Content	Description	Number of Repetitions	Time (s)
Weeks 1–2	Ankle pump exercise	Maximal dorsiflexion for 5 s followed by plantarflexion for 5 s	120	5
	Quadriceps contraction	Forceful contraction of anterior thigh muscles for 5 s, then relax for 2 s	15	5
	Hamstring contraction	With knee fully extended, press down forcefully on a pillow placed under the heel	15	5
	Straight leg raise	Lift leg 15–60° off the bed, hold until exhaustion	10	10
	Knee extension exercise	Place a pillow under the heel, leaving the knee unsupported; relax muscles completely; mild posterior knee discomfort is normal	2	1,800
	Range of motion exercise	Seated beside bed with leg hanging; flex knee to target angle and hold for 10 min	1	300
	Weight shift training	Forward-backward and side-to-side directions	10	3
	Single-leg stance balance exercise	Stand straight, arms at sides, lift the affected foot and maintain balance	120	5
Week 3	Ankle pump exercise	Maximal dorsiflexion for 5 s followed by plantarflexion for 5 s	15	5
	Quadriceps contraction	Forceful contraction of anterior thigh muscles for 5 s, then relax for 2 s	15	5
	Hamstring contraction	With knee fully extended, press down forcefully on a pillow placed under the heel	10	10
	Straight leg raise	Lift leg 30–60° off the bed, hold until exhaustion	2	1,800
	Knee extension exercise	Place a pillow under the heel, leaving the knee unsupported; relax muscles completely; mild posterior knee discomfort is normal	2	1,800
	Range of motion exercise	Seated beside bed with leg hanging/seated pushing against wall; flex knee to target angle and hold	1	300
	Single-leg stance balance exercise	Stand straight, arms at sides, lift the affected foot and maintain balance	120	5
	Stepping exercise	Stand straight, hands at sides, march in place	1	180
	Walking exercise	Walk in front of a mirror, correcting abnormal gait patterns	1	180
Week 4	Straight leg raise	Lift leg 30–60° off the bed, hold until exhaustion	2	1,800
	Knee extension exercise	Place a pillow under the heel, leaving the knee unsupported; relax muscles completely; mild posterior knee discomfort is normal	2	1,800
	Range of motion exercise	Seated beside bed with leg hanging/seated pushing against wall; flex knee to target angle and hold	1	300
	Single-leg stance balance exercise	Stand straight, arms at sides, lift the affected foot and maintain balance	120	5
	High-knee marching exercise	Stand straight, hands at sides, march with high knees	1	180
	Walking exercise	Walk in front of a mirror, correcting abnormal gait patterns	1	300
Week 5	Resisted straight leg raise	With knee extended, lift leg 30–60° off the bed using an elastic band, hold until exhaustion	2	1,800
	Weighted knee extension exercise	Place a pillow under the heel, leaving the knee unsupported; relax muscles completely; a sandbag may be placed above the knee; mild posterior knee discomfort is normal	2	1,800
	Range of motion exercise	Seated, hold the knee to chest; flex to target angle and hold	1	300
	Single-leg stance balance exercise	Stand straight, arms at sides, lift the affected foot and maintain balance	120	5
	Step-up with healthy leg support	Healthy leg supports; affected leg rests on step, slowly perform stepping-up motion	15	3
	Reverse lunge with healthy leg	Stand straight with hands on hips, affected leg flexed at 90°, healthy leg steps back and kneels down	15	5
	High-knee marching exercise	Stand straight, hands at sides, march with high knees	1	300
	Walking exercise	Walk in front of a mirror, correcting abnormal gait patterns	2	300
Week 6	Resisted straight leg raise	With knee extended, lift leg 30–60° off the bed using an elastic band, hold until exhaustion	2	1,800
	Knee extension exercise	Place a pillow under the heel, leaving the knee unsupported; relax muscles completely; a sandbag may be placed above the knee; mild posterior knee discomfort is normal	2	1,800
	Range of motion exercise	Seated, hold the knee to chest; flex to target angle and hold	1	300
	Single-leg stance balance exercise	Stand straight, arms at sides, lift the affected foot and maintain balance	120	5
	Stepping exercise	Stand straight, hands at sides, march in place	1	180
	Step-down with affected leg support	Affected leg stands on step maintaining balance; healthy leg lowers down, touching the floor gently with the heel	15	3
	Reverse lunge with healthy leg	Stand straight with hands on hips, affected leg flexed at 90°, healthy leg steps back and kneels down	15	5
	Fast walking exercise	Walk in front of a mirror, correcting abnormal gait patterns	1	300
Week 7	Bilateral squat angle training	Symmetrical weight-bearing on both lower limbs; train knee flexion angle and lower limb strength through squatting	1	900
	Backward step-up with affected leg support	Affected leg performs single-leg support; healthy leg steps backward onto a step	20	3
	Supine weighted straight leg raise	Supine, lift straight leg upward with resistance provided by a sandbag	15	10
	Prone weighted hamstring curl	Prone, flex the knee against resistance provided by a sandbag	15	10
	Wall squat exercise	Squat against a wall in a pain-free range; ensure knees do not extend beyond toes	5	40
	Forward lunge with affected leg	Stand straight with hands on hips, healthy leg flexed at 90°, affected leg steps back and kneels down	5	5
	Fast walking exercise	Walk in front of a mirror, correcting abnormal gait patterns	2	300
Week 8	Bilateral squat angle training	Symmetrical weight-bearing on both lower limbs; train knee flexion angle and lower limb strength through squatting	1	900
	Supine weighted straight leg raise	Supine, lift straight leg upward with resistance provided by a sandbag	15	10
	Prone weighted hamstring curl	Prone, flex the knee against resistance provided by a sandbag	15	10
	Wall squat exercise	Squat against a wall in a pain-free range; ensure knees do not extend beyond toes	5	40
	Fast walking exercise	Walk in front of a mirror, correcting abnormal gait patterns	2	300
Weeks 9–3 months	Wall squat exercise	Squat against a wall in a pain-free range; ensure knees do not extend beyond toes	5	40
	Bilateral countermovement jump	Squat bilaterally then jump upward and land	15	3
	Single-leg countermovement jump (affected side)	Squat on affected leg then jump upward and land	10	3
	Standing resisted leg raise with elastic band	Standing, perform leg raises in multiple directions against elastic band resistance	15	10
	Fast walking exercise	Walk in front of a mirror, correcting abnormal gait patterns	2	300

### Statistical analysis

The primary analysis will employ a mixed-effects model to account for within-subject correlations across repeated measures during the 2-year follow-up and to handle potentially missing data at random. All statistical tests will be performed with a significance level set at *α* = 0.05. A repeated-measures two-way analysis of variance (ANOVA) will be used to evaluate the interaction effects between group (experimental vs. control) and time (baseline, 3 months, 6 months, 1 year, and 2 years) on cartilage biochemical characteristics derived from functional MRI (T1*ρ*/T2 values) and on gait parameters. For multiple comparisons, the Bonferroni correction will be applied. For EMG data, repeated-measures ANOVA will be used to assess the differences in muscle activation patterns before and after gait retraining, thereby exploring the neuromuscular control mechanisms underlying the effects of gait retraining on gait biomechanics. To control the false discovery rate (FDR) when comparing MRI parameters across 10 cartilage subregions and multiple time points, the FDR method will be applied with the threshold set at 0.05. Missing data will be assumed to be missing at random (MAR) and will be addressed using the mixed-effects model without imputation or deletion. For the analysis populations, the primary analysis will follow the intention-to-treat (ITT) principle, including all participants as originally randomized. Sensitivity analysis will be performed using a per-protocol (PP) set, including only participants who completed the full intervention and all follow-up assessments. Effect sizes will be reported as partial eta-squared (*η*^2^). Outliers, defined as values exceeding ±3 standard deviations from the group mean, will be excluded and reanalyzed in a sensitivity analysis.

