**Methods:**

This study is a single-blind, parallel-group randomized controlled trial. A total of 60 participants scheduled for primary unilateral ACLR will be recruited and randomly allocated to either the experimental group (conventional rehabilitation plus gait retraining) or the control group (conventional rehabilitation only). Gait retraining will commence at 3 weeks post-surgery, lasting for 6 weeks with a frequency of 2–3 sessions per week, each lasting 15–20 min. Data will be collected at baseline (pre-intervention) and at 3 months, 6 months, 1 year, and 2 years postoperatively. Assessment will include three-dimensional gait analysis, surface electromyography (sEMG), isokinetic muscle strength testing, functional magnetic resonance imaging (fMRI), Y-balance test, single-leg hop test, the International Knee Documentation Committee (IKDC) subjective knee evaluation form, Lysholm knee score, and Tegner activity scale. The primary outcome measure is the peak knee flexion moment during walking. Secondary outcomes include cartilage T1*ρ*/T2 values, muscle activation patterns, and subjective functional scores. A repeated-measures analysis of variance (ANOVA) will be used to evaluate the intervention effects on the outcome measures.

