### Participants and recruitment

#### Sample size calculation

The primary outcome measure is the peak knee flexion moment during walking, a key biomechanical indicator of cartilage degeneration (21). A significant difference in this measure will be considered statistically meaningful. Based on preliminary results, the mean peak knee flexion moment before training in ACLR patients is 0.20 BW·BH, with a standard deviation of 0.09. After training, the mean peak knee flexion moment is 0.28 BW·BH, with a standard deviation of 0.11 Nm/kg/m. Using the formula for sample size estimation for two independent samples, $n=\frac{2\sigma^{2}{\left(Z_{\alpha /2}+Z_{\beta }\right)}^{2}}{\delta^{2}}$, with *α* = 0.05 and *β* = 0.2,among $\sigma =\sqrt[{2}]{\frac{\sigma_{1}^{2}+\sigma_{2}^{2}}{2}}$, $\delta =\bar{X_{1}}-\bar{X_{2}}$, the required sample size for each group was calculated to be 25.Accounting for a 20% dropout rate, 30 participants per group will be recruited. The required sample size corresponds to a Cohen's d of 0.8, indicating a large effect size.

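### The primary outcome falls under both a mixed-effects model, labelled primary, and a repeated-measures ANOVA with no stated role; run classically, the ANOVA would break the plan's ITT and no-deletion rules

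*Protocol article*

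**What the plan says.** The Sample size calculation section fixes the primary outcome: "The primary outcome measure is the peak knee flexion moment during walking, a key biomechanical indicator of cartilage degeneration". The Statistical analysis section then makes these statements in one paragraph:

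- Primary method: "The primary analysis will employ a mixed-effects model to account for within-subject correlations across repeated measures during the 2-year follow-up".
- Group-by-time test: "A repeated-measures two-way analysis of variance (ANOVA) will be used to evaluate the interaction effects between group (experimental vs. control) and time", with baseline and all four follow-ups listed as the levels of time. The outcomes covered are the T1rho/T2 values "and on gait parameters".
- Missing data: "Missing data will be assumed to be missing at random (MAR) and will be addressed using the mixed-effects model without imputation or deletion".
- Population: "the primary analysis will follow the intention-to-treat (ITT) principle, including all participants as originally randomized".
- The per-protocol set, used for sensitivity analysis, holds those who finished the intervention and attended every follow-up.
- Partial eta-squared is the effect size to be reported.

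The Methods part of the abstract names one method only: "A repeated-measures analysis of variance (ANOVA) will be used to evaluate the intervention effects on the outcome measures". It does not mention a mixed model.

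**The concern.** Peak knee flexion moment during walking is a gait parameter, so the paragraph covers the primary outcome twice, by two different methods. Nothing marks the ANOVA as secondary, supportive or a sensitivity analysis, and nothing says that it is a test taken from the mixed model.

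The two methods differ in whom they analyse. A likelihood-based mixed model uses every visit that was observed. A classical repeated-measures ANOVA needs the full set of five measurements, and its complete-case result is in general protected only if data are missing completely at random. That is a stronger condition than the one the plan adopts.

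At stake are which participants count in the main result, whether the intention-to-treat claim can be honoured, and whether someone could choose between two published methods after seeing the data. A later analysis plan cannot settle this quietly, because either choice would depart from a sentence in this article.

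**Working it through.** **1. The statements side by side**

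| Rule in the plan | Mixed model, all available data | Classical repeated-measures ANOVA, five visits |
|---|---|---|
| Missing at random | Consistent | In general needs missing completely at random |
| No imputation, no deletion | Consistent | Drops anyone with a missed visit |
| All randomized participants | Consistent, given at least one usable measurement | Only those with all five measurements |
| Per-protocol set as a separate sensitivity analysis | Distinct set | Differs only by participants who attended every visit but did not complete the intervention |

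**2. The plan's own sample size, reproduced**

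Inputs from Sample size calculation: means 0.20 and 0.28, standard deviations 0.09 and 0.11, α = 0.05 two-sided, β = 0.2.

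- σ = √((0.09² + 0.11²)/2) = 0.1005; δ = 0.08; d = 0.08/0.1005 = 0.796.
- n = 2σ²(1.96 + 0.84)²/δ² = 24.77 (unrounded normal quantiles), so 25 per group. The stated figure reproduces, and 25 × 1.2 = 30 per group recruited.

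**3. Classical ANOVA at the documented 20% dropout**

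- Complete cases are at most 30 × 0.80 = 24 per group, or 48 of 60.
- Power for the planned two-sample contrast by the plan's normal approximation, Φ(d√(n/2) − 1.96), is 80.4% at n = 25 and 78.7% at n = 24.
- By the t-test it is 78.7% at n = 25 and 77.0% at n = 24.
- Either way the difference is under 2 percentage points.

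**4. Range under an assumption**

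The document gives no per-visit rate. Assume that a share m of participants miss each of the four follow-up visits, independently, and that this is the only loss. Complete cases are then 60(1 − m)⁴, and 30(1 − m) per group are seen at any one follow-up visit. Power is by the same normal approximation.

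| m (assumed) | (1 − m)⁴ | Complete of 60 | Power, complete cases | Seen at one visit, per group | Power at that visit |
|---|---|---|---|---|---|
| 2% | 0.922 | 55.3 | 84.2% | 29.4 | 86.3% |
| 5% | 0.815 | 48.9 | 79.5% | 28.5 | 85.2% |
| 10% | 0.656 | 39.4 | 70.4% | 27.0 | 83.3% |

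A per-visit rate of 1 − 0.80^(1/4) = 5.4% would by itself bring complete cases down to 80%. The last column uses everyone seen at one visit under the same missingness, so it is a fairer comparator than the n = 25 target. These powers describe a single two-sample contrast, not the five-visit interaction test under either method, and serve only to show the order of size.

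**The case against.** The strongest reply is that the plan does name a primary method. The mixed model is the only one that carries the label, and the missing-data rule is tied to it: "addressed using the mixed-effects model without imputation or deletion". On that reading, the ANOVA sentence is shorthand for the group-by-time F-test from the mixed model, and the abstract is a condensed summary. If so, the conflict disappears. This part of the reply stands: listwise deletion belongs to the classical ANOVA and is not something the plan states. A reader might infer that the plan will delete every participant with one missed visit. The document does not support that as a fact, only as the consequence of one way of carrying out the sentence.

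A reader might also infer a large power loss by adding 5% missed per visit to the full dropout: 30 × 0.80 × 0.95⁴ = 19.5 per group, with t-test power falling from 79% at n = 25 to 68%. This is not supported either. The 5% is not in the document, nothing there says it comes on top of the 20%, and the n = 25 target is not what a mixed model would achieve under the same missingness.

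Partial eta-squared is a separate reporting matter: naming one metric does not mean that mean differences will go unreported. Nor does the contradiction depend on a particular covariance structure or set of baseline terms, which can be left to the analysis plan.

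The reply does not remove the contradiction. The document never says that the ANOVA is the mixed model's test, and the ANOVA-only abstract and the ANOVA effect size point the other way.

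**Conclusion.** The point holds as a contradiction in the stated text, not as missing detail. The primary outcome sits under a mixed model labelled primary and under a repeated-measures ANOVA of unstated role, and the abstract gives only the latter. The breach of the intention-to-treat and no-deletion rules is conditional on the ANOVA being run in its classical form.

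On the documented 20% dropout, that form would keep at most 24 of 30 per group, and the planned contrast would lose under 2 percentage points of power against n = 25. If missed visits at 5% to 10% per follow-up were the only loss, about 49 to 39 of 60 participants would be complete. Those rates are assumed. The contradiction stands whatever the rates are, and it should be settled before anyone sees outcome data by group.

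**What to change.** 1. In Statistical analysis, name the mixed-effects model (group, visit, group-by-visit, all available data) as the single primary analysis of peak knee flexion moment, and use it for the other gait parameters and T1rho/T2.
2. Remove the repeated-measures ANOVA for these outcomes, or state that the group-by-time test is the F-test from the mixed model.
3. Change the abstract to match.
4. Report the between-group mean difference with a 95% confidence interval at each visit, because partial eta-squared alone gives neither direction nor units.

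Adjusting for the baseline value, which is already collected, is an optional addition. The cost is a text change in two places, with no change to data collection or sample size.

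### The sample size is set for one two-group comparison at alpha 0.05, but the only test stated for the primary outcome is a group-by-time interaction over five time levels with Bonferroni follow-up, so the stated 80% power does not belong to the stated test

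*Protocol article*

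**What the plan says.** **Sample size calculation.** "The primary outcome measure is the peak knee flexion moment during walking". The inputs are a value before training ("the mean peak knee flexion moment before training in ACLR patients is 0.20 BW·BH, with a standard deviation of 0.09") and a value after it ("After training, the mean peak knee flexion moment is 0.28 BW·BH, with a standard deviation of 0.11 Nm/kg/m"). The method is given as "Using the formula for sample size estimation for two independent samples", with alpha 0.05 and beta 0.2, and "the required sample size for each group was calculated to be 25". Adding for 20% dropout gives 30 per group. The formula has no term for visits, within-patient correlation or multiplicity, and no visit is named.

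**Statistical analysis.** The section opens by calling a mixed-effects model the primary analysis but does not say which contrast from it is tested. It then assigns gait parameters and cartilage T1ρ/T2 values to a two-way repeated-measures ANOVA of the group-by-time interaction, with the levels "time (baseline, 3 months, 6 months, 1 year, and 2 years"). It adds: "For multiple comparisons, the Bonferroni correction will be applied". It does not say how many comparisons the correction covers.

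**Abstract.** A repeated-measures ANOVA is also named there as the means of evaluating the intervention effects.

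**The concern.** A sample size is valid for the test it was derived for. Here the derivation concerns one difference between two means. The test written down for the same outcome is a joint test with 4 degrees of freedom, in which the baseline value is one more outcome level. Its power depends on the correlation between visits and on how the effect evolves over two years, and neither enters the calculation.

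The interaction also does not say at which visit the groups differ. With four postoperative visits, none primary, and an unspecified Bonferroni family, success on the primary outcome has no single definition, and a claim could settle on whichever visit looks favourable.

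**Working it through.** **1. The plan's own figure.** Inputs from the sample size section: δ = 0.28 − 0.20 = 0.08; σ² = (0.09² + 0.11²)/2 = 0.0101, so σ = 0.1005 and d = 0.08/0.1005 = 0.796.

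n = 2σ²(1.960 + 0.842)²/δ² = 24.77, so 25 per group. The figure reproduces as one unadjusted two-sided comparison. The powers below use 24 per arm (30 less 20%) unless stated otherwise.

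**2. The interaction actually described.** Five time levels and two groups give 4 numerator df and 4(2n − 2) = 184 denominator df at n = 24. Compound symmetry with correlation ρ is an assumption, because the article gives no correlation. The noncentrality is

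λ = (n/2) · Σ(δₜ − δ̄)² / [σ²(1 − ρ)]

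where δₜ is the group difference at visit t and δ̄ its mean over the five levels.

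- Sustained effect (0, δ, δ, δ, δ): Σ = 0.8δ². At ρ = 0.3, λ = 12 × 0.8 × 0.0064/(0.0101 × 0.7) = 8.69.
- Waning effect (0, δ, 0.75δ, 0.5δ, 0.25δ): Σ = 0.625δ². At ρ = 0.3, λ = 6.79.
- Difference at 1 year only (0, 0, 0, δ, 0): Σ = 0.8δ², the same as for the sustained effect.

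Power at alpha 0.05 (noncentral F):

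| Effect profile | ρ = 0.3 | ρ = 0.5 | ρ = 0.7 |
|---|---|---|---|
| Sustained, 24 per arm | 63% | 80% | 96% |
| 1 year only, 24 per arm | 63% | 80% | 96% |
| Waning to 25%, 24 per arm | 51% | 68% | 90% |
| Sustained, 30 per arm | 75% | 89% | 99% |

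The first two rows are equal: the test cannot tell a benefit lasting two years from an isolated difference at one visit.

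**3. Bonferroni-corrected visit comparisons.** The size of the family is not stated. If it were the four postoperative visits (an assumption), each test would run at 0.05/4 = 0.0125. By noncentral t with d = 0.796 and no baseline adjustment, power at one named visit is 57% at 24 per arm, 59% at 25 and 69% at 30. It is 78.9% at 36 and 80.3% at 37, so 37 per arm would be needed for 80%. These figures do not depend on ρ.

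**4. One baseline-adjusted contrast at one visit.** Adjustment for a baseline value with correlation r to the outcome turns d into d/√(1 − r²). At 24 per arm, two-sided 0.05, noncentral t:

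| r (assumed) | 0 | 0.3 | 0.5 | 0.7 |
|---|---|---|---|---|
| Effective d | 0.796 | 0.834 | 0.919 | 1.115 |
| Power | 77% | 81% | 88% | 97% |

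At each correlation from 0.3 to 0.7, this is at least as powerful as the interaction in step 2 with the same 24 patients per arm.

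**The case against.** The strongest reply is that the primary analysis is the mixed model, not the ANOVA. The ANOVA sentence covers gait and MRI outcomes together and is not labelled as the primary test; the contrast, visit and covariates may stand in a fuller document. This stands in part. Reading the interaction as the primary test is an inference, though the natural one, since no other test is stated for this outcome. It also means that one cannot assert that the mixed model leaves baseline unadjusted; the article is silent on that. What the article does state still does not match its sample size.

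Second, underpowering is not shown. This stands. At ρ of 0.5 or more with a sustained effect, the interaction has about 80% power or better, and 24 per arm is cautious because a mixed model also uses patients who miss some visits.

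Third, the four-visit Bonferroni family is not in the article, follow-up tests do not reduce the power of an omnibus test, and a rule that accepts any one of the four visits would have more power than 57%. All of this stands, so the figures in step 3 are conditional and apply to one named visit.

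Fourth, some criticisms a reader might add fail. Any two-sided test can be significant in the wrong direction, and direction is read from the estimate. Keeping baseline as a repeated response is valid under randomisation; adjusting for it gains precision but corrects no error.

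Last, the gain from adjustment is not guaranteed. The eligibility section has baseline data collected before surgery, and a preoperative value may predict gait after reconstruction only weakly. Hence the range for r starts at 0, where power is 77%.

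**Conclusion.** The point holds as a mismatch. The article claims 80% power for one comparison, states a 4-df interaction for the same outcome, and leaves the mixed model's contrast and the primary visit open. The interaction's power at 24 per arm runs from 51% to 96% over the assumed correlations (0.3 to 0.7) and the sustained and waning profiles. The claimed 80% is therefore neither confirmed nor refuted by what is written.

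A reader might infer that the trial is underpowered, or that it needs 37 per arm. The article does not support either: the first depends on a correlation and an effect profile it does not give, and the second on a Bonferroni family it does not define. Confidence is high for the mismatch and the missing definition of success, not for a power shortfall.

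**What to change.** Before outcome data are analysed:

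- State the primary test as one between-group difference in peak knee flexion moment from the mixed model, at one named visit, adjusted for the baseline value (or with baseline constrained equal across arms), at two-sided alpha 0.05.
- Let the sponsor choose the visit. Three months is the first assessment after the 6-week programme and best matches the post-training value used for sizing; a later visit is legitimate if the effect assumed there is justified.
- Make the remaining visits secondary, and confine Bonferroni to secondary gait comparisons with their number stated.
- Restate the power for this contrast, giving the assumed baseline correlation and its source. At 24 per arm it ranges from 77% (r = 0) to 97% (r = 0.7).

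The cost is a change of text and a short recalculation; the data are already planned. The small downside is that the other visits become secondary, which narrows the primary claim in a trial with two years of follow-up.

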## Methods

### Study design

This study is a prospective randomized controlled trial. The experimental group will undergo gait training in addition to standard rehabilitation, while the control group will receive only standard rehabilitation. Both groups will be assessed at baseline, 3 months, 6 months, 1 year, and 2 years postoperatively (Figure 1).

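### Single-step Bonferroni is valid for the gait follow-up contrasts, but Holm's step-down procedure is never less powerful at the same family-wise error and would be a near-free improvement

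*Protocol article*

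**What the plan says.** Under Study design, the protocol article sets four postoperative assessments after baseline: "Both groups will be assessed at baseline, 3 months, 6 months, 1 year, and 2 years postoperatively". The Statistical analysis section plans a group-by-time analysis over these time points for gait parameters and for T1ρ/T2 values, and the next sentence reads: "For multiple comparisons, the Bonferroni correction will be applied". No step-down version, family or number of comparisons is given. The overall level is fixed by "All statistical tests will be performed with a significance level set at *α* = 0.05". Later in the same section, MRI comparisons over 10 cartilage subregions and several time points are given a separate rule, FDR at 0.05. Effect sizes are to be partial eta-squared, and simultaneous confidence intervals are not mentioned.

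The Sample size calculation section sizes the trial for one two-group comparison of peak knee flexion moment, "with *α* = 0.05 and *β* = 0.2", with no allowance for multiplicity.

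**The concern.** With K comparisons, Bonferroni holds every one of them to 0.05/K. Holm orders the p-values and tests them in turn at 0.05/K, 0.05/(K−1), and so on up to 0.05, stopping at the first that fails. Once one contrast is established, the rest face a milder threshold.

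The difference matters most when several contrasts are truly non-null together. A trial that follows gait for 2 years has reason to care about that case. Because the sample size covers a single test at 0.05, any correction comes straight out of power, so it is worth using the correction that takes least.

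**Working it through.** **1. The plan's own figure.** Inputs, from the Sample size calculation section: "the mean peak knee flexion moment before training in ACLR patients is 0.20 BW·BH, with a standard deviation of 0.09" and "After training, the mean peak knee flexion moment is 0.28 BW·BH, with a standard deviation of 0.11 Nm/kg/m".
- δ = 0.28 − 0.20 = 0.08
- σ² = (0.09² + 0.11²)/2 = 0.0101, so σ = 0.1005
- d = 0.08/0.1005 = 0.796
- n = 2 × 0.0101 × (1.960 + 0.842)² / 0.08² = 24.77, which rounds up to 25

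This agrees with "the required sample size for each group was calculated to be 25". With 30 recruited and the stated 20% dropout, 30 × 0.8 = 24 per group remain.

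**2. Why Holm dominates, for any K above 1.**
- *It rejects at least as much.* If a p-value is at or below 0.05/K, so is every smaller one, and each Holm threshold is at least 0.05/K. Holm therefore rejects whatever Bonferroni rejects.
- *It gives the same control.* With m₀ true null hypotheses, the first one Holm could wrongly reject has rank at most K − m₀ + 1, so it meets a threshold of at most 0.05/m₀. The chance that any of m₀ true-null p-values falls that low is at most m₀ × 0.05/m₀ = 0.05, whatever the dependence.

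**3. Size of the gain.** Assumptions that are not in the plan: K = 4 (one between-group contrast at each postoperative visit), equal correlation between visits of 0.3 to 0.7, complete data on 24 per group, and two-sample t-tests in place of the mixed model. The Bonferroni threshold is 0.05/4 = 0.0125 throughout. The Holm thresholds are 0.0125, 0.0167, 0.025 and 0.05. Results are from simulation, 20,000 to 40,000 trials per setting.

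| Effect pattern, 24 per group | Power at | Bonferroni | Holm |
|---|---|---|---|
| 0.796 SD at all four visits | each visit | 56–57% | 66–67% |
| Full at 3 and 6 months, half at 1 and 2 years (correlation 0.5) | 1 and 2 years | 12% | 19% |
| At one visit only | that visit | 56–57% | 56–57% |

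With a constant effect and 30 per group, power per visit is about 69% against 77–80%. If the 6-month effect has already fallen to three quarters, the Holm figure at 2 years is about 18% instead of 19% (24 per group, correlation 0.5).

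**4. What does not change.** With no effect at any visit, family-wise error is identical for the two methods (about 3.5–4.6% at 24 per group). The chance of at least one significant visit is also identical, because both methods test the smallest p-value at 0.05/K. It is about 79–91% at 24 per group with a constant effect.

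**The case against.** The strongest reply is that nothing here is wrong. Bonferroni is standard and valid, the section does not contradict itself by naming it, and preferring Holm could be called taste. The validity stands. The charge of taste does not, because the plan names a method that another one dominates without any added assumption.

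Several limits of scope also stand:
- The four-visit family is the natural inference from where the sentence sits, but the plan does not state it. The dominance holds for any family; the figures do not.
- MRI comparisons across subregions and time points already have their own rule, so the point does not reach the cartilage comparisons placed under FDR.
- The planning effect is a before/after-training difference, and nothing in the plan supports its full persistence to 2 years.
- The t-tests on completers only approximate the planned mixed model, which uses all available data.
- Bonferroni has simple matching simultaneous intervals and Holm does not. The article mentions none, but interval reporting may be left to an analysis plan that is not shown.

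A reader might infer that the trial gives up its power to show a lasting effect and gets nothing in return. Under a constant effect, the chance of significance at all four visits is indeed 19–33% with Bonferroni and 41–54% with Holm. The documents do not support that reading. No section makes significance at every visit the criterion for success. If it were the criterion, each visit could be tested at 0.05 with no correction, and Holm would not be the remedy either.

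**Conclusion.** The point holds as an optional, cheap improvement. For the comparisons left under Bonferroni, chiefly follow-up contrasts on gait parameters and the primary outcome among them, Holm is at least as powerful at the same family-wise 0.05.

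The gain is about 10 percentage points per visit if the planning effect is present at all four visits, about 7 points at 1 and 2 years if it halves there (from a level that is low under either method), and practically nil if only one visit shows an effect. These sizes rest on the assumed family of four, the assumed correlations and 24 completers per group. The dominance rests on none of them. The plan's error control and its overall group-by-time test are not in question.

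**What to change.** Replace the Bonferroni sentence in the Statistical analysis section with, for example:

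> For the four postoperative between-group contrasts on each gait outcome, the Holm step-down procedure will be applied at a family-wise level of 0.05 and Holm-adjusted p-values reported; MRI subregion and time-point comparisons use the FDR method stated below.

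Naming the family is part of the fix, since Holm's thresholds are undefined without it. As worded, control applies within each gait outcome and not across them. The change should be made before outcome data are seen, so that it cannot look data-driven.

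It costs no patients, visits or procedures. The small downside is that unadjusted confidence intervals would stand beside the adjusted p-values, and the report should say so.
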